### Outcomes of the study {12}

The schedule of enrolment, interventions, and assessments for the study is shown in Table 1. The primary outcomes are body weight, body mass index (BMI), serum albumin, and pre-albumin level. The secondary outcomes include energy and protein intake, muscle and fat mass, handgrip strength, haemoglobin, serum transferrin, high sensitivity C-reactive protein (hs-CRP), interleukin-6 (IL-6), salivary cortisol, sleep quality, length of hospital stay, and postoperative complication rate within 30 and 90 days after surgery. The changes for these parameters will be assessed at a day prior to discharge (V3), 30 days after surgery (V4), and 90 days after surgery (V5) compared to baseline as shown in Table 2.

**Table 2 Tab2:** Outcome parameters’ description

Domain	Specific measurements	Metric and time points for assessment	Method of aggregation
Primary outcomes			
Nutrition status	Body weight, kg	Change from baseline (V1) at1 day prior to discharge (V3); change from 1 day prior to discharge (V3) at 30 days after surgery (V4); change from 1 day prior to discharge (V3) at 90 days after surgery (V5)	Mean
	BMI, kg/m^2^		
	Serum albumin, g/L		
	Serum prealbumin, mg/L		
Secondary outcomes			
Nutrition status	Handgrip strength, kgF	Change from baseline (V1) at 1 day prior to discharge (V3); change from 1 day prior to discharge (V3) at 30 days after surgery (V4); change from 1 day prior to discharge (V3) at 90 days after surgery (V5)	Mean
	Muscle mass, kg		
	Fat mass, kg		
	Serum transferrin, g/L		
	Haemoglobin, g/dL		
Inflammation	High-sensitivity C-reactive Protein (hs-CRP), mg/L		Mean
	Interleukin-6 (IL-6), pg/ml		
	Salivary cortisol, μg/dL		
Dietary intake	Energy intake, kcal/d		Mean
	Protein intake, g/d		
Sleep quality	Pittsburgh Sleep Quality Index (PSQI) score		Median
Postoperative complications	Postoperative complications	Frequency of postoperative complications at discharge (V3), at 30 days after surgery (V4), and 90 days after surgery (V5)	Median
	Length of hospital stay	Number of days of hospitalisation from admission (V1) to 1 day before discharge (V3)	Median

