### Sample size calculation {14}

The sample size required is calculated based on the improvement in serum albumin level. To detect a between-group difference of at least 4g/L of serum albumin level that would cause approximately 25% reduction in morbidity among patients who have serum albumin in the normal range (around 38 g/L) [36], and a standard deviation of 6.5g/L, at 80% power and with a 5% alpha error. A minimum of 23 subjects per group is required. After accounting for a 20% drop-out rate, 28 subjects are required per group and thus a total of 84 subjects will be recruited in the three groups.

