## Assignment of interventions: allocation

### Randomisation {16a}

This is an open-labelled study and randomisation is performed using computer-generated software [37] by personnel not involved in the data collection. Patients are randomised into one of the three intervention arms in the ratio of 1:1:1 without stratification by study sites. The randomisation is done through the block method whereby the block size is either 3, 6, or 9 to minimise predictability and selection bias.

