## Statistical methods

### Statistical methods for primary and secondary outcomes {20a}

Statistical analyses will be performed using the Statistical Package for the Social Science software (SPSS version 26, IBM, USA). The normality of the data will be evaluated using Shapiro-Wilk’s test. Normally distributed data will be expressed as mean and standard deviation. Skewed data will be described using median with interquartile range for skewed data. Categorical data will be expressed in count and percentages. Evaluation of outcomes will be carried out by both intention-to-treat and per-protocol analyses. The primary analysis will take a per protocol approach and the secondary analysis an intention-to-treat (ITT) approach. The per protocol analysis will include patients who fully completed the intervention allocated and attended all visits (‘complete cases’ approach). The primary analysis will employ repeated measures ANOVA (RMANOVA) to assess for time × group interactions. A secondary analysis of difference between groups for continuous variables will be conducted by using analysis of covariance (ANCOVA), controlling for baseline or at discharge values. The ITT approach will include all patients who are randomised to the three groups, irrespective of dropouts. In order to perform RMANOVA using the ITT approach, missing data will be imputed with the last observation carried forward method using the last available data point from the patients. ANCOVA will be restricted to per-protocol basis. *P*-value <0.05 is considered statistically significant for all tests.

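### For the baseline-to-discharge albumin contrast, the primary RMANOVA is less efficient than the baseline-adjusted ANCOVA that the plan already holds but makes secondary and confines to per-protocol patients

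*Protocol article*

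**What the plan says.** Section {20a} of the protocol article sets the primary analysis: "The primary analysis will employ repeated measures ANOVA (RMANOVA) to assess for time × group interactions". It is run on per-protocol complete cases. The section names no covariate and does not say which visits form the time factor.

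The same section plans an ANCOVA adjusting for the baseline or the discharge value, but as a secondary analysis, and adds: "ANCOVA will be restricted to per-protocol basis". The only analysis of all randomised patients is the RMANOVA with last observation carried forward. No reason is given for keeping ANCOVA out of it.

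Table 2 in section {12} lists four primary outcomes: weight, BMI, albumin and prealbumin. Each has three contrasts: V3 against V1, V4 against V3, and V5 against V3. The study design section {8} lists five visits, baseline included.

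Section {14} sizes the trial on albumin: "To detect a between-group difference of at least 4g/L of serum albumin level", with "a standard deviation of 6.5g/L, at 80% power and with a 5% alpha error". It does not say whether the SD belongs to a single measurement or to a change, and it gives no correlation between visits.

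**The concern.** The plan holds two ways of comparing arms on the same data and gives the deciding role to the one that, for a matched two-visit contrast, is less precise. A change score subtracts the whole baseline value. ANCOVA subtracts only the part that predicts the outcome. Unless the correlation is very high, the change score therefore carries extra noise. It also over-corrects a chance baseline difference between arms, through regression to the mean, and such differences can be sizeable with 23 to 28 patients per arm.

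At stake is the chance of detecting a real albumin or prealbumin effect at discharge, and the width of its interval. The per-protocol restriction adds to this. ANCOVA needs only the reference value and the visit value, so nothing in the method calls for patients who completed everything. As written, a reader who wants a baseline-adjusted estimate for all randomised patients will not find one.

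**Working it through.** **Inputs.** From section {14}: difference 4 g/L, SD 6.5 g/L, alpha 5% (taken as two-sided), 23 evaluable per group and 28 recruited. Assumed: the correlation rho between V1 and V3, shown from 0.3 to 0.9, and equal variance at both visits.

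**The plan's own figure first.** The stated requirement is: "A minimum of 23 subjects per group is required". The usual two-group formula gives 2 × (1.96 + 0.84)² × 6.5² / 4² ≈ 41.5, so 42 per group. With 23 per group, the two-sided two-sample t-test has 53% power (55% by the normal approximation). A one-sample or paired t-test with SD 6.5 does need 23 for 80%, but that is not the between-group comparison described. The figure of 23 therefore does not reproduce for the stated comparison.

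**The matched V1-to-V3 contrast.** With V1 and V3 as the time levels, the time × group test is an analysis of V3 − V1.

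- Change-score variance: 2(1 − rho)σ²
- ANCOVA variance: (1 − rho²)σ²
- Ratio, ANCOVA to change: (1 − rho)(1 + rho) / [2(1 − rho)] = (1 + rho)/2, which is below 1 for every rho below 1

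At rho 0.5 the change-score SD is 6.5 × √1 = 6.5 and the ANCOVA SD is 6.5 × √0.75 = 5.63. Pairwise power by noncentral t, reading 6.5 as the SD of a single value:

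| rho | variance ratio | change score, 23 per arm | ANCOVA, 23 per arm | gain (points) |
|---|---|---|---|---|
| 0.3 | 0.65 | 41% | 57% | 16 |
| 0.4 | 0.70 | 46% | 61% | 14 |
| 0.5 | 0.75 | 53% | 65% | 12 |
| 0.6 | 0.80 | 63% | 72% | 10 |
| 0.7 | 0.85 | 75% | 82% | 6 |
| 0.8 | 0.90 | 90% | 93% | 3 |
| 0.9 | 0.95 | above 99% | above 99% | about 0 |

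At 28 per arm the change is 62% to 74% at rho 0.5 and 83% to 89% at rho 0.7. If 6.5 is instead the SD of a change, the gain at 23 per arm is about 18 points at rho 0.3, 12 at 0.5, 7 at 0.7 and 4 at 0.8.

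**Five-visit check.** Section {20a} does not fix the time levels, so the interaction was also simulated over all five visits: three arms, 23 per arm, equal correlation of 0.5 between visits, and an effect of 4 g/L.

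| Effect pattern | RMANOVA interaction | ANCOVA at V3 on V1 | Mean of V3 to V5, adjusted for V1 |
|---|---|---|---|
| SS and SS-E both raised from V3 to V5 | 76% | 65% | 92% |
| SS and SS-E raised at V3 only | 53% | 66% | 18% |
| SS raised at V3 only, SS-E from V3 to V5 | 87% | about 65% | 82% |

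No method leads in every row. These tests also address different hypotheses, so the table does not rank them for one question.

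**The case against.** The strongest reply is that the two-visit loss describes an analysis the plan may not run. With five visits, the interaction test can match or beat a single-visit ANCOVA, as the first and third rows of the second table show. The third row is close to the contrast that the SS and SS-E arms exist to test. This stands. A reader might infer that the trial as a whole loses a fixed 12 points of power. The documents do not support that: the figure needs rho = 0.5, which appears nowhere in them, and a two-level time factor, which {20a} does not specify.

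A reader might also infer that the V1 values go unused. They do not. If V1 is a time level, the interaction already contrasts each patient with baseline, in both the per-protocol and the all-randomised analysis. The test remains valid under randomisation. What is at issue is efficiency.

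Two limits also stand. The gain is negligible for weight and BMI, two of the four primary outcomes, on the assumption that they correlate very highly between visits. The power figures cover V1 to V3 only. SS and SS-E are treated alike up to discharge, so these figures say nothing about extended supplementation.

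The objection does not explain why ANCOVA is withheld from the all-randomised analysis. Nor does it change the algebra for the contrast that Table 2 lists first.

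**Conclusion.** The point holds for the matched contrast. For albumin at V3 against V1, ANCOVA on V1 is never less efficient than the change-score test apart from the one degree of freedom it spends. At 23 per arm the pairwise power given up is about 16 points at rho 0.3, 12 at 0.5, 6 at 0.7 and 3 at 0.8. This assumes equal variances, a two-sided 5% test and 6.5 g/L as the SD of a single value. Prealbumin follows the same variance ratio, but the plan gives no inputs for its power.

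The per-protocol restriction on ANCOVA is a separate weakness that does not depend on rho. No reason is stated for it, and it leaves every all-randomised analysis without baseline as a covariate.

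A reader might hope that adjustment rescues the sample size. It cannot be relied on to do so. At rho 0.5, 23 per group reaches only 65%, and about 80% would need rho near 0.68. The shortfall against the stated 80% is a sample-size matter in its own right.

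**What to change.** In {20a}:

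1. For each contrast in Table 2, make the between-arm comparison an ANCOVA of the visit value on arm, with the matching reference value as covariate. For V3 that is V1. For V4 and V5, keep the V3-adjusted version for the discharge-anchored metric that Table 2 states, and add V1 as the covariate instead if the effect since randomisation is wanted. V3 is measured after the arms have diverged before surgery, so the two versions answer different questions for comparisons with DS. The text should say which is meant.
2. Delete the sentence restricting ANCOVA to per-protocol patients, and run it on all randomised patients who have the reference and visit values.
3. Keep the RMANOVA time × group test as supportive, and list the visits in its time factor.

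With the reference value as covariate, the arm effect is the same whether the response is the visit value or the change, so Table 2 can stand. The cost is one degree of freedom and protocol or SAP wording. The data are already collected and the ANCOVA is already planned, so no patients, visits or assays are added. The sample-size statement in {14} needs its own correction.

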### Interim analyses {21b}

Not applicable as analyses will only be done upon the completion of this study.

### Methods for additional analyses (e.g. subgroup analyses) {20b}

Not applicable and no plan for additional analyses.

### Methods in analysis to handle protocol non-adherence and any statistical methods to handle missing data {20c}

The ITT approach will include all patients who are randomised to the three groups, irrespective of dropouts. In order to perform RMANOVA using the ITT approach, missing data will be imputed with the last observation carried forward method using the last available data point from the patients.

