### Study design {8}

This study is a multi-centre, open-label, multi-arm, parallel-group randomised controlled trial at two tertiary hospitals. This protocol is written in accordance with the Standard Protocol Items: Recommendations for Interventional Trials (SPIRIT) checklist. The schedule of enrolment, interventions, and assessments for the duration of the study is tabulated in Table 1. Patients enrolled in the study are randomised into 3 arms and followed up at baseline, a day prior to surgery, a day prior to discharge, 30 days after surgery, and 90 days after surgery (Fig. 1).

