Our study considers serum albumin and prealbumin level as primary outcomes. Both albumin and prealbumin are visceral proteins and negative acute phase reactants whereby the latter has a shorter half-life (2–3 days) to detect more acute changes. They have been routinely used for monitoring disease progression in the inpatient setting and as an indirect measure of nutrition and postoperative morbidity and mortality rate [55]. Serum albumin is recognised as a powerful predictor for cancer survival in many types of cancer [56, 57] and it has numerous implications towards postoperative complications and length of hospital stay [55, 58]. One RCT study suggested that the provision of ONS may be able to stabilise the declined serum albumin and total protein during the postoperative period [47]. More studies are required to understand the extent of serum albumin and prealbumin level response to nutrition intake despite the metabolic alteration occurring among cancer patients.

Our study also measures the effects of ONS on body composition alongside the surgical and biochemical outcomes that are monitored perioperatively. Bruns et al. highlighted that current intervention studies are heterogenous in defining nutritional status and thus are not sufficient to capture the whole picture of malnutrition [21]. BMI alone does not reflect body composition. Cancer patients can present loss of muscle mass defined as sarcopenia despite having a high BMI [59]. Excessive body fat is correlated to the chronic inflammatory response in cancer [60] and low muscle mass is linked with poor disease prognosis [61]. It is noteworthy that the results extrapolated from our study can form a basis for future research to determine the prevalence of sarcopenic obesity and also the changes of body composition among this population during the disease trajectory to identify the crucial period for nutrition intervention.

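### The only planned analysis of all randomised patients uses last observation carried forward, which scores anyone last seen by V3 as unchanged afterwards and shrinks a real late difference

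*Protocol article*

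**What the plan says.** Sections {20a} and {20c} of the protocol article both fix the method: "missing data will be imputed with the last observation carried forward method using the last available data point from the patients". Section {20a} gives the reason in the words that introduce it: "In order to perform RMANOVA using the ITT approach". No argument is offered that a patient's values stay constant after leaving.

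The roles of the analyses are also fixed:
- Ranking, in section {20a}: "The primary analysis will take a per protocol approach and the secondary analysis an intention-to-treat (ITT) approach".
- Completers only, with nothing imputed, in the analysis ranked first: "The per protocol analysis will include patients who fully completed the intervention allocated and attended all visits".
- Everyone randomised in the analysis ranked second: "The ITT approach will include all patients who are randomised to the three groups, irrespective of dropouts".
- Covariate-adjusted comparisons for completers only: "ANCOVA will be restricted to per-protocol basis".

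Taken together, repeated measures ANOVA (RMANOVA) on carried-forward data is the only analysis of all randomised patients that the article names.

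Section {8} has patients "followed up at baseline, a day prior to surgery, a day prior to discharge, 30 days after surgery, and 90 days after surgery" (V1 to V5). Table 2 in section {12} measures V3 as change from V1, and V4 and V5 as change from V3. Section {6b} gives post-discharge supplementation to SS-E only. Sections {11b} and {22} withdraw patients who have a serious adverse event (SAE).

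**The concern.** Last observation carried forward (LOCF) assumes that nothing changes after the last visit attended. Here the visits straddle an operation, and the Discussion describes albumin and prealbumin as negative acute phase reactants. It also cites one trial suggesting that supplementation may "stabilise the declined serum albumin and total protein during the postoperative period". No change is a poor assumption for such markers over 90 days of recovery.

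It is also the wrong assumption for the question asked. What distinguishes SS-E from the other arms after discharge can arise only after V3, which is where LOCF sets change to zero.

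The ITT result is the one check on the selection built into a completers-only primary analysis. If it is distorted by when patients leave, agreement or disagreement between the two analyses cannot be interpreted.

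**Working it through.** The plan gives no figure for the effect of LOCF, so there is none to reproduce. Inputs from section {14}: target difference 4 g/L, SD 6.5 g/L, drop-out 20%, 28 per arm. The V3-to-V5 recovery and the arm-specific drop-out rates are not in the document; where used, they are assumptions.

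**What LOCF assigns, using Table 2's definitions**
- Last seen at V1: the V3, V4 and V5 changes are all zero.
- Last seen at V2: the V3 change is V2 − V1; the V4 and V5 changes are zero.
- Last seen at V3: the V4 and V5 changes are zero.
- Last seen at V4: the V5 change equals the V4 change.

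**Formula.** Let c be the true mean change from V3 to V5 in an arm and d the share last seen at or before V3, with leaving unrelated to outcome. The LOCF mean change is (1 − d) × c, so the estimated difference is (1 − d1) × c1 − (1 − d2) × c2. For patients lost after V3, the V5 level gives the same difference if the arms share a V3 mean, because that mean cancels. This matters because the text of section {12} speaks of change from baseline while its Table 2 uses V3.

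**Equal drop-out, true difference of 4 g/L arising after V3.** (1 − 0.20) × 4 = 3.2 g/L, a 20% attenuation whatever the common recovery.

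**Equal drop-out, no true difference.** c1 = c2 and d1 = d2, so the difference is 0.

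**Unequal drop-out, no true difference.** With common recovery R, the bias is (d2 − d1) × R. In absolute size:
- gap 0.10: R = 3, 5, 8 gives 0.3, 0.5, 0.8 g/L
- gap 0.20: R = 3, 5, 8 gives 0.6, 1.0, 1.6 g/L

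Against 4 g/L this is 7.5% to 40%. The sign depends on which arm loses more patients.

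**Unequal drop-out, true difference of 4 g/L, R = 6 in the comparator** (so 10 in SS-E)
- SS-E 10%, comparator 30%: 0.9 × 10 − 0.7 × 6 = 4.8 g/L
- SS-E 30%, comparator 10%: 0.7 × 10 − 0.9 × 6 = 1.6 g/L

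**Simulation.** 4,000 runs, 28 per arm, SD 6.5, assumed V3–V5 correlation 0.6, V3 mean 6 g/L below the comparator's V5 mean, drop-out after V3 completely at random, two-sample t-test on the V5 level:

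| True difference | Drop-out, SS-E / comparator | LOCF estimate | LOCF rejection | Observed-only estimate | Observed-only rejection |
|---|---|---|---|---|---|
| 0 | 20% / 20% | 0.0 | 5.4% | 0.0 | 5.4% |
| 0 | 10% / 30% | 1.2 | 9.9% | 0.0 | 4.9% |
| 0 | 30% / 10% | −1.2 | 9.7% | 0.0 | 4.6% |
| 4 | 20% / 20% | 3.3 | 38.6% | 4.0 | 53.2% |
| 4 | 10% / 30% | 4.8 | 68.9% | 4.0 | 50.7% |
| 4 | 30% / 10% | 1.6 | 12.6% | 4.0 | 50.4% |

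This illustrates the mechanism with a simpler test than RMANOVA. The observed-only power is itself well below 80%, which is a separate sample-size matter.

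**Precision.** LOCF counts 28 values per arm where 28 × 0.8 = 22.4 are observed. Assuming equal variances, the nominal standard error is √0.8 = 0.89 of the one the observed V5 values support, about 11% smaller. With equal drop-out and no true difference this did not by itself inflate the error rate (5.4% in the table).

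**The case against.** **LOCF does not touch the primary analysis.** True. A reader might infer that the headline result is biased by imputation; the document does not support that, since the primary analysis is per protocol without filled values. What stands is that the only all-randomised analysis is affected.

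**The loss may be the same in every arm.** Section {14} plans one 20% rate, and all arms have the same visits. It is tempting to say that SS-E, with the longest regimen, will lose more patients and be penalised. The document gives no arm-specific rates, and loss could as well be higher in DS. No direction can be claimed. The attenuation to 3.2 g/L needs no imbalance.

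**Early and late drop-out might cancel.** A reader might infer that patients lost before surgery, who carry a value without a surgical fall, bias V4/V5 the opposite way. On Table 2's metric they do not: they too are scored as zero change from V3. An opposite effect could appear at V3, or at V5 measured against baseline if V5 were still below baseline, which the document does not state.

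**The postoperative fall and recovery are not quantified.** Correct. The Discussion reports a hedged result from one cited trial and gives no depth at V3 or recovery by day 90. The 3 to 8 g/L is an assumed range.

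**The bias is small against sampling error.** The standard error of a two-arm difference is 6.5 × √(2/28) = 1.74 g/L, larger than 0.3 to 1.6 g/L. That limits the practical size. Even so, a 1.2 g/L bias roughly doubled the simulated type I error.

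**LOCF is conservative.** Only sometimes: 4.8 g/L for a true 4 g/L is not conservative.

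**Conclusion.** The point holds in a limited form. LOCF is a poor choice for the secondary ITT analysis, and the article fixes it rather than leaving it open.

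The firmest figure is the attenuation of a true 4 g/L difference to about 3.2 g/L. It rests on the planned 20% drop-out, equal across arms, all after V3 with no V4 or V5 data, unrelated to outcome, and on a difference that arises after V3. With equal drop-out and no true difference there is no bias in the contrast.

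The 0.3 to 1.6 g/L bias, in either direction, depends on assumed unequal drop-out and assumed recovery and should be read as a range of possibilities. The SAE withdrawal rule makes outcome-related drop-out plausible, since SAEs include hospitalisation or its prolongation; its effect cannot be sized from the document.

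The sponsor should make this change, but it does not undermine the primary analysis as defined.

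**What to change.** For the ITT analysis, replace RMANOVA on carried-forward data with a likelihood-based mixed model for repeated measures on every observed visit of every randomised patient. Include arm, visit and arm × visit with an unstructured covariance. Model V1 as a response rather than a covariate, so that patients seen only at V1 stay in. Estimate the V3-to-V4 and V3-to-V5 changes, and their differences between arms, as contrasts within the model. This removes the stated reason for LOCF, because the model does not need complete rows.

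The model assumes data are missing at random, which the SAE withdrawals put in doubt. Add a multiple-imputation sensitivity analysis with delta adjustment, with the range of deltas set before the data are analysed, and drop LOCF.

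Cost: recruitment is under way, so this is a protocol amendment to be reported to the ethics committee under section {25}, plus a little more analysis work. Visits and sample size do not change. Section {21b} puts all analysis at study completion, so the change can be dated before any results are seen, which matters because the analysts are not blinded (section {17a}).
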